### **4.3. Prohibitions and Restrictions**

Potential subjects must be willing and able to adhere to the following prohibitions and restrictions during the course of the study to be eligible for participation.

Significant teratogenic and/or embryocidal effects have been shown in animals exposed to RBV. Ribavirin may persist in non-plasma compartments for as long as 6 months. It is contraindicated in women who are pregnant or breastfeeding and in male partners of women who are pregnant. In addition, extreme care must be taken to avoid pregnancy in female subjects and in female partners of male subjects taking RBV for at least 6 months after completion of PegIFN $\alpha$ -2a/RBV therapy (or longer, if dictated by local regulations). Ribavirin should not be started unless a report of a negative pregnancy test is obtained immediately prior to initiation of therapy. Therefore, the following precautions must be adhered to:

1. A woman of childbearing potential who is heterosexually active must remain on two different highly effective methods of birth control (see inclusion criteria in Section 4.1) from screening and up to 6 months after the last dose of RBV (or longer if dictated by local regulations).
2. A woman using oral contraceptives must use an additional birth control method (see inclusion criterion in Section 4.1).
3. A man who is sexually active with a woman of childbearing potential and has not had a vasectomy must agree to use two different highly effective methods of birth control (including at least one barrier method). A man who is sexually active with a woman of childbearing potential and has had a vasectomy must agree to use a barrier method of birth control e.g., either condom with spermicidal foam/gel/film/cream/suppository or partner with occlusive cap (diaphragm or cervical/vault caps) with spermicidal foam/gel/film/cream/suppository. All men must also not donate sperm during the study and for 6 months (or longer if dictated by local regulations) after the last dose of RBV.

For male subjects, it is the responsibility of the subject to ensure that his partner (or partners) is (are) not pregnant prior to entry into the study or becomes pregnant during the treatment and post-therapy follow-up phase of the study. During treatment with RBV, female partners of male participants should follow the guidelines as outlined in the manufacturer's prescribing information for RBV.

4. Subjects should be informed that during TMC435 administration photosensitivity reactions (rash confined to sun-exposed areas) have been reported and should be informed on the importance of sun protection during TMC435 treatment. Extreme exposure to the sun or sunbathing should be avoided, as well as the use of tanning devices (e.g., sunbed, solarium) from baseline until the last intake of TMC435.

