## Footnotes

a Duration of follow-up after early withdrawal will depend on the planned duration of treatment (see Section 3.1):

- subjects who prematurely discontinue all study medication before Week 8 will be followed until Week 36.
- subjects who would have qualified for a total treatment duration of 12 weeks but prematurely discontinued after Week 8 will be followed until Week 36.
- subjects who would have qualified for total treatment duration of 24 weeks but prematurely discontinued after Week 8 will be followed until Week 48.
- subjects who discontinue treatment because they meet a virologic stopping rule at Week 4 or Week 12 will be followed until Week 36.
- subjects who discontinue treatment due to viral breakthrough will be followed until 4 weeks after withdrawal (i.e., they will come back for visits at time of discontinuation and 4 weeks after study medication withdrawal)

- b The first scheduled visit (every 12 weeks from baseline) after study medication withdrawal will not be performed if it coincides (with a time window of  $\pm 7$  calendar days) with the Week 4 visit after study medication withdrawal. In such a case, every effort should be made to ensure that for subsequent visits the schedule every 12 weeks from baseline is adhered to.
- c Free thyroxine (T4) and free triiodothyronine (T3) will be assessed if TSH is abnormal.
- d The biochemistry sample at 12-weekly intervals (counting from baseline) must be taken after fasting for at least 10 hours. It is recommended that biochemistry samples at all other time points also be taken after fasting for at least 10h. The homeostasis model assessment for insulin resistance (HOMA IR) index will be derived from insulin and glucose (fasted) test results at 12-weekly intervals (counting from baseline).
- e Urinalysis performed locally by dipstick. If there are clinically relevant abnormalities in the investigator's opinion, further urinalysis should be done locally (e.g., sediment analysis including RBC, WBC, casts). Clinically relevant findings from local urinalysis will be reported as AEs.
- f Urine test for women of childbearing potential. Extra pregnancy test kits will be given if more than 4 weeks between two consecutive study visits to perform a pregnancy test at home.
- g Sequencing of the HCV NS3/4A region will be done at the discretion of the Study Responsible Scientist.

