- Not of childbearing potential: postmenopausal (> 45 years of age with amenorrhea for at least 12 months or any age with amenorrhea for at least 6 months and a serum follicle stimulating hormone (FSH) level > 40 IU/mL); permanently sterilized (e.g., tubal occlusion, hysterectomy, bilateral salpingectomy); or otherwise be incapable of pregnancy,
- Of childbearing potential and practicing two different highly effective methods of birth control (including at least one barrier method) consistent with local regulations regarding the use of birth control methods for subjects participating in clinical studies: e.g., established use of oral, injected or implanted hormonal methods of contraception; placement of an intrauterine device (IUD) or intrauterine system (IUS); barrier methods: condom with spermicidal foam/gel/film/cream/suppository or occlusive cap (diaphragm or cervical/vault caps) with spermicidal foam/gel/film/cream/suppository; male partner sterilization (the vasectomized partner should be the sole partner for that subject); true abstinence (when this is in line with the preferred and usual lifestyle of the subject).

Note: If the childbearing potential changes after start of the study (e.g., woman who is not heterosexually active becomes active, premenarchal woman experiences menarche) a woman must begin 2 highly effective methods of birth control, as described above.

9. A woman must have a negative serum  $\beta$ -human chorionic gonadotropin ( $\beta$ -hCG) test at screening and women of childbearing potential must have a negative urine pregnancy test before first dose of study drug.
10. A man who is sexually active with a woman of childbearing potential and has not had a vasectomy must agree to use two different highly effective methods of birth control (including at least one barrier method). A man who is sexually active with a woman of childbearing potential and has had a vasectomy must agree to use a barrier method of birth control e.g., either condom with spermicidal foam/gel/film/cream/suppository or partner with occlusive cap (diaphragm or cervical/vault caps) with spermicidal foam/gel/film/cream/suppository. All men must also not donate sperm during the study and for 6 months (or longer if dictated by local regulations) after the last dose of RBV.
11. Subject must be willing and able to adhere to the prohibitions and restrictions specified in this protocol.

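### Section 4.3 names 6 months after ribavirin for male subjects' partners, but the operative rules for men give birth control no end date and end the partner-pregnancy duty with study follow-up

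*Protocol*

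**What the plan says.** The opening paragraph of Section 4.3 gives a reason and a period. The reason is that "Ribavirin may persist in non-plasma compartments for as long as 6 months". The period covers both sexes: "extreme care must be taken to avoid pregnancy in female subjects and in female partners of male subjects taking RBV for at least 6 months", counted from the completion of PegIFN/RBV, or longer where local rules require it. The numbered precautions are introduced as following from this.

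- **Item 1 (women).** Two methods of birth control, "from screening and up to 6 months after the last dose of RBV". This rule is dated.
- **Item 3 (men).** Two methods for a man without a vasectomy, or a barrier method for a man with one, if he is sexually active with a woman of childbearing potential. Neither limb has an end date. The 6 months in item 3 belongs to the ban on sperm donation.
- **Inclusion criterion 10 (Section 4.1).** Same content as item 3: the man "must agree to use two different highly effective methods of birth control (including at least one barrier method"), and again only sperm donation is dated.
- **Partner-pregnancy sentence (after item 3).** The male subject must ensure that no partner is pregnant at entry or "becomes pregnant during the treatment and post-therapy follow-up phase of the study".

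Section 3.1 sets follow-up at 24 weeks after the last planned dose. Section 9.1.4 makes 24 weeks a minimum but exempts withdrawal of consent and viral breakthrough. Footnote a of Time and Events Schedule Part 4 says that "subjects who discontinue treatment due to viral breakthrough will be followed until 4 weeks after withdrawal".

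**The concern.** One section describes the same duty in two ways. The opening paragraph runs it for at least 6 months after therapy. The sentence addressed to the man himself runs it to the end of his study follow-up. Item 3, which should settle the matter as item 1 does for women, is silent on duration. Section 4.3 also introduces its restrictions as applying during the course of the study, which makes the shorter reading easier to adopt.

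A site that follows the dated sentence literally would treat a man's obligation as finished before the period that the Protocol itself links to ribavirin persistence has passed. What is at stake is possible fetal exposure. No endpoint, sample size or analysis is touched.

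**Working it through.** **Inputs**

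- Follow-up: 24 weeks after the last planned dose (Section 3.1).
- Last visits: Week 36 after 12 weeks of treatment, Week 48 after 24 weeks (Section 10.1).
- Follow-up after viral breakthrough: 4 weeks from withdrawal (Schedule Part 4, footnote a).
- Follow-up after stopping before Week 8, or after a Week 4 or Week 12 virologic stopping rule: to Week 36 (same footnote).
- Comparison period: 6 months (opening of Section 4.3). Counted from every start date over two years, 6 calendar months last 181 to 184 days.

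**Reproducing the stated follow-up.** 36 − 12 = 24 weeks and 48 − 24 = 24 weeks. Both agree with Section 3.1, and 24 × 7 = 168 days.

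**Shortfall = 6 calendar months − days from stopping to the last follow-up visit**

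| Situation | Days followed | Against 181–184 days |
|---|---|---|
| Completer, 12 or 24 weeks | 24 × 7 = 168 | 13 to 16 short |
| Completer, last visit 2 days late (window in Section 9.1.1) | 170 | 11 to 14 short |
| Viral breakthrough | 4 × 7 = 28 | 153 to 156 short |
| Stopped at Week 12 by stopping rule | (36 − 12) × 7 = 168 | 13 to 16 short |
| Stopped at Week 8 | (36 − 8) × 7 = 196 | none (12 to 15 over) |
| Stopped at Week 4 by stopping rule | (36 − 4) × 7 = 224 | none (40 to 43 over) |

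Stopping before Week 8 gives more than 196 days, so there is no shortfall there either. Withdrawal of consent has no fixed follow-up, so no figure can be given.

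**Other passages that bear on men**

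- Section 1.5.4 includes males with a female partner of childbearing potential in its at-least-6-months statement, but refers back to Section 4.3 for the methods.
- Exclusion criterion 13 (Section 4.2) excludes a man who plans to father a child within 6 months of the last RBV dose. It screens plans at entry and sets no duration for contraception.

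These passages agree with the opening of Section 4.3. Criterion 10 and item 3 are silent, and the partner-pregnancy sentence stops earlier.

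**The case against.** The best reply is that the 6 months for men is already there. The opening of Section 4.3 is in mandatory terms and governs the items beneath it, and Section 1.5.4 and exclusion criterion 13 point the same way. On this view item 3 is incomplete drafting, and the partner-pregnancy sentence assigns responsibility during the study without saying that precautions stop afterwards. Much of this stands: the intention is clear, and a careful reader would find it. It does not remove the inconsistency, because women have a dated rule, men do not, and the only date addressed to the man himself is a different one.

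The 28-day figure also depends on a reading. If the follow-up phase means the 24 weeks after the last planned dose in Section 3.1 for everyone, a man with breakthrough would be at most 13 to 16 days short. Section 9.1.4, however, expressly exempts viral breakthrough from the 24 weeks, so the shorter reading has textual support.

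Four stronger readings are tempting, and the Protocol does not support them:

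- **That there is no 6-month provision for men.** Three passages contain one.
- **That virologic failures in general leave early.** Only viral breakthrough has the 4-week schedule. Stopping rules at Week 4 and Week 12 lead to follow-up until Week 36.
- **That the rule on stopping study medication for contraception failure (Sections 1.5.5 and 10.2) gives this gap consequences.** The gap falls after treatment, when there is no medication left to stop.
- **That the number of men affected can be estimated.** The Protocol gives neither the share of men nor a breakthrough rate, and item 3 covers only men sexually active with a woman of childbearing potential.

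**Conclusion.** The point holds as an internal inconsistency in Section 4.3, shared by criterion 10. Taken literally, the dated sentence ends a man's duty 13 to 16 days before 6 calendar months for completers and about 153 to 156 days before after viral breakthrough. Men stopped at Week 4, or before Week 8, have no shortfall.

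The figures assume that months are calendar months, that visits fall on schedule, and that the follow-up phase means the subject's own follow-up. The inconsistency itself rests on none of these. For most men the gap is about two weeks, and the long gap is confined to one route out of the study. The consent form and the ribavirin prescribing information were not available, so what men are actually told cannot be checked here. The correction is still worth making, because it bears on fetal safety and costs almost nothing.

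**What to change.** The sponsor should reconcile the opening paragraph of Section 4.3, item 3, the partner-pregnancy sentence, inclusion criterion 10, Section 1.5.4 and exclusion criterion 13, and decide on one period for men. That end date should then be written out in three places: criterion 10, item 3 (both the two-method limb and the barrier limb after vasectomy) and the partner-pregnancy sentence, where it replaces the reference to the follow-up phase. It should not depend on how long a subject is followed. It should also name its starting event, since the opening paragraph counts from completion of PegIFN/RBV and item 1 from the last RBV dose. Which period applies is for the sponsor to determine.

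The cost is one phrase in two criteria and one revised sentence, checked against the consent form. No visits, procedures or analyses are added.

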## 5. TREATMENT ALLOCATION AND BLINDING

Randomization will not be used in this study. All subjects will be assigned to the same treatment. Duration of treatment will be response-guided (see Section 3.1).

In an attempt to enroll similar percentages of the 3 host *IL28B* genotypes (CC, CT or TT) as were enrolled in the ongoing TMC435 Phase 3 studies, the sponsor will make all effort to respect the following maximum caps for enrolment of each *IL28B* genotype for subjects with genotype 1 or genotype 4 HCV infection separately:

- a maximum of 35% of subjects with host *IL28B* genotype CC (i.e., maximum 35% *IL28B* CC among subjects with genotype 1 HCV infection and maximum 35% *IL28B* CC among subjects with genotype 4 HCV infection);
- a maximum of 55% of subjects with host *IL28B* genotype CT (i.e., maximum 55% *IL28B* CT among subjects with genotype 1 HCV infection and maximum 55% *IL28B* CT among subjects with genotype 4 HCV infection);
- a maximum of 18% of subjects with host *IL28B* genotype TT (i.e., maximum 18% *IL28B* TT among subjects with genotype 1 HCV infection and maximum 18% *IL28B* TT among subjects with genotype 4 HCV infection).

In addition, within subjects infected with genotype 1 HCV, the sponsor seeks a balance between HCV genotypes 1a and 1b, therefore all effort will be made to cap enrolment of HCV genotype 1a at:

- a maximum of 50% of subjects infected with HCV genotype 1a.

Procedures to manage the distribution of the HCV genotype 1 subtypes and the *IL28B* subtypes will be communicated to the investigators at study initiation.

As this is an open-label study, blinding procedures are not applicable.

## 6. DOSAGE AND ADMINISTRATION

### 6.1. Treatment Overview and Response-Guided Treatment Duration

All subjects will receive triple therapy consisting of TMC435 plus PegIFN $\alpha$ -2a and RBV for 12 weeks. Total anti-HCV treatment duration will be response-guided based on HCV RNA levels at Week 2, Week 4, and Week 8 as follows:

- Subjects will qualify for a total treatment duration of only 12 weeks (ie all anti-HCV treatment is discontinued after week 12) if the following criteria are met: HCV RNA value is
  - < 25 IU/mL (detectable or undetectable) at Week 2,  
AND
  - < 25 IU/mL undetectable at Week 4,  
AND
  - < 25 IU/mL undetectable at Week 8.
- if HCV RNA is above the threshold defined above at any of the 3 time points, subjects will continue PegIFN $\alpha$ -2a and RBV until Week 24.

The above treatment continuation criteria will at all times be overruled if a subject meets any of the virologic stopping criteria outlined in Section 6.3.

Table 1 provides an overview of treatment dosage.

The HCV RNA samples will be processed in real-time and results will be communicated to the investigators and sponsor throughout the study.

The investigator will make treatment decisions in line with these treatment duration criteria and virologic stopping criteria (as mentioned in Section 6.3).

**Table 1: Treatment Overview**

| Subjects and timing                                                                                                                                                                                                                                                                                                                                                          | Treatment and Dosage                                                                                                                                                                                                                  | Number of capsules/volume                                                                                                                                                                                                               |
|------------------------------------------------------------------------------------------------------------------------------------------------------------------------------------------------------------------------------------------------------------------------------------------------------------------------------------------------------------------------------|---------------------------------------------------------------------------------------------------------------------------------------------------------------------------------------------------------------------------------------|-----------------------------------------------------------------------------------------------------------------------------------------------------------------------------------------------------------------------------------------|
| All subjects
stop all therapy after Week 12 if
HCV RNA < 25 IU/mL (detectable or undetectable) at Week 2 AND
< 25 IU/mL undetectable at Week 4 AND
< 25 IU/mL undetectable at Week 8;
otherwise continue treatment in Extension                                                                                                          |                                                                                                                                                                                                                                       |                                                                                                                                                                                                                                         |
| Week 1 (Day 1) to Week 12 (Day 84) (inclusive)                                                                                                                                                                                                                                                                                                                               | 
 
• TMC435: 150 mg q.d., oral
 
• PegIFN<math>\alpha</math>-2a: 180 <math>\mu</math>g once weekly, SC
 
• RBVa: 1000 mg or 1200 mg in a b.i.d. regimen, oral
 
 | 
 
• TMC435: one 150-mg capsule
 
• PegIFN<math>\alpha</math>-2a: 1 SC injection of 0.5 mL
 
• RBV: 200-mg tablets as needed according to the subject's weighta
 
 |
| Treatment extension
If HCV RNA at Week 2, 4 and 8 does not meet the above-outlined criteria for treatment stop at Week 12, continue treatment as follows:                                                                                                                                                                                                          |                                                                                                                                                                                                                                       |                                                                                                                                                                                                                                         |
| Week 13 (Day 85) to Week 24 (Day 168) (inclusive)                                                                                                                                                                                                                                                                                                                            | 
 
• PegIFN<math>\alpha</math>-2a: 180 <math>\mu</math>g once weekly, SC
 
• RBVa: 1000 mg or 1200 mg in a b.i.d. regimen, oral
 
                                      | 
 
• PegIFN<math>\alpha</math>-2a: 1 SC injection of 0.5 mL
 
• RBV: 200-mg tablets as needed according to the subject's weighta
 
                                       |
| SC: subcutaneous
a RBV dosage is weight-based:
Body weight < 75 kg: total daily dose is 1000 mg, administered as 400 mg (2 tablets of 200 mg, morning intake) and 600 mg (3 tablets of 200 mg, evening intake);
Body weight $\geq$ 75 kg: total daily dose is 1200 mg, administered as 2 x 600 mg (3 tablets of 200 mg per intake, morning and evening). |                                                                                                                                                                                                                                       |                                                                                                                                                                                                                                         |

